### 4.2 Inclusion and exclusion criteria

To be eligible, study participants must meet the following criterium:

- Non-pregnant or (first trimester) pregnant women of reproductive age (18-49 years old), without a previous diagnosis of type 1 diabetes or T2DM (confirmed by a random glucose test, which is a random blood test to check the glucose levels at random and no fasting condition is required. This test will be carried out by pricking the fingertip with a lancet and glucometer to all women during the recruitment).

Potential participants meeting any of the following criteria will not be enrolled in the study:

- Pregnant women with active GDM
- Adult males, and children and adolescents <18 years old of both sexes
- Pre-existent severe chronic conditions (e.g. chronic liver or kidney disease, chronic obstructive pulmonary disease (COPD))
- Living outside of the surrounding catchment areas of the 6 healthcare centers.
- Women internationally displaced, without a permanent home or identified physical address. This to decrease the possibility of drop-outs.
- Women planning to move elsewhere in the following 2 years
- Women that do not provide a written IC.

### 4.3 Sample size

The present study is based on a three-level hierarchical design where two groups of 3 healthcare centers (matched in population size and geographical area, urban/rural) will be randomized to the intervention and comparison group, and healthcare workers within the same cluster provide the intervention allocated to the participants

The sample size will be based on the expected differential change in the primary outcome of the study (healthy lifestyle score) determined by the questionnaire developed and validated in India by Dubasi and co-workers to assess the adherence to dietary and physical activity advice for weight control in lifestyle-related diseases. The questionnaire's total score ranges between 14-65 points, a lower score indicates poor adherence to a healthy lifestyle, while a higher score indicates good adherence.

In this cRCT, 1 group of 3 healthcare centers will be randomly allocated to the intervention group and the other group of 3 healthcare centers to the comparison group. A comparable study measuring also lifestyle behavior changes as primary outcome, and using a similar score scale has reported a differential improvement from baseline to follow-up after 35 weeks of 20% between intervention and comparison groups. Also, literature has reported intra-class correlation (ICC) coefficients for interventions concerning dietary and physical activity improvements range in between 0.007-0.3.

Based on this previous evidence and the demographics of our study setting, the following assumptions have been used to approximate a power calculation estimate. This calculation was done using STATA version 16 for a cluster-randomized design assuming a realistic number of participants sample from each healthcare center whereby the following parameters were considered:

- 48 participants per cluster (144 participants per intervention program)
- Improvement of 12% in the lifestyle questionnaire score between intervention and comparison group (+ 6 score points)
- Effect size of 0.7 (score of the average person in the experimental group is 0.7 standard deviations above the average person in the comparison group, thus surpasses the scores of 69% of the comparison group).
- ICC of 0.1
- 20% loss to follow up and no attrition expected

Based on the above and considering a 95% level of significance (one-sided p-value), a power of 91% to detect the effect size is achieved. The possibility of an entire cluster withdrawal was also considered. Based on the previous parameters and 1 cluster dropped (2 intervention clusters and 3 comparison clusters or vice versa), a power of 85% would be reached.

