| DESIGN                                     | KIS-Antwerp will be implemented and evaluated using a matched cluster-randomized controlled trial involving 6 healthcare centers in Kisantu from where women will be recruited into two study groups: an intervention group and a comparison group.                                                                                                                                                                                                                                                                                                                                                                                                                      |
| STUDY SITE & POPULATION                | The study will take place in 6 healthcare centers across Kisantu, Democratic Republic of Congo (DRC) and will be limited to women of reproductive age (18-49 years) irrespectively of pregnancy status. A total of 144 participants per arm necessary to detect a 12% change in the primary outcome with a level of significance of 0.05, power >80%, and considering a 20% loss of follow-up.                                                                                                                                                                                                                                                                           |
| DURATION                                   | The duration of the present study is 24 months.                                                                                                                                                                                                                                                                                                                                                                                                                                                                                                                                                                                                                          |

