##### **Evaluation study design**

A cluster randomized controlled trial (cRCT) with a hierarchical design will be conducted whereby 2 groups of 3 healthcare centers (in total 6 healthcare centers) will be randomized to an intervention group or comparison group. The intervention group will be provided with the intervention program based on educational + motivational strategies whereas the comparison group will be limited to a basic educational strategy only (**Figure 1**). This design allows us to provide all women with proven effective preventive strategy (education) while testing for a comprehensive approach (education + motivation). The intervention program will last 24 months, starting approximately in September 2021 until September 2023 (Timeline of the study is presented in **Annex 2**).

The intervention program components and topics covered by the intervention group entail the following: Individualized education, group activities (group education and physical activity sessions), goal setting, use of pedometer, and community activities (if possible in the second year of intervention). In contrast, the components compromised in the comparison group are limited to basic individualized education at baseline only. Further information regarding the intervention program components and topics is presented in **Annex 3**.

[figure not shown]

**Figure 1.** Study design and intervention program components

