### 8.3 Statistical methods

#### 8.3.1 Analysis populations

The analyses will be conducted based on the intention-to-treat principle. A probability of <0.05 will be considered statistically significant for all tests. All analyses will be conducted using STATA (Release 16/SE. College Station, TX: StataCorp LP) by ITM's staff.

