On average conditions, meaning 30 participants per cluster, change of 12%, ICC of 0.1 and SD of 7 points, a power of 89% would be reached. However, if one cluster withdrawal the power would decrease to 82%, borderline to detect a change with enough power. Hence, to ensure power considering a withdrawal of 1 cluster, sample size calculation presented in section 4.3 entails 40 participants per cluster plus 20% loss to follow, indicating 144 participants per arm (total of 288 participants enrolled in the study) are needed to detect a change of 12% (with ICC 0.1 and SD of 7) between the intervention and comparison group with a level of significance of 95%.

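### The stated 91% power (85% with one centre lost) reproduces only with a normal test; allowing for six centres, the same inputs give about 79% and 66% one-sided

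*Combined protocol and SAP*

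**What the plan says.** The protocol's Evaluation study design says that "2 groups of 3 healthcare centers (in total 6 healthcare centers) will be randomized". Section 4.3 lists "48 participants per cluster (144 participants per intervention program"), a difference of 6 points, an effect size of 0.7, an ICC of 0.1 and 20% loss to follow-up. It concludes that, "considering a 95% level of significance (one-sided p-value), a power of 91% to detect the effect size is achieved". For the loss of a centre it says: "1 cluster dropped (2 intervention clusters and 3 comparison clusters or vice versa), a power of 85% would be reached".

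Section 8.4 gives the inputs in full: 40 women per centre before the 20% allowance, SD 7, ICC 0.1 and a 6-point difference. It reports that with 30 per centre, "ICC of 0.1 and SD of 7 points, a power of 89% would be reached", falling to 82% if a centre withdraws. It gives that drop as the reason for moving to 40 per centre.

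The synopsis summarises this as "level of significance of 0.05, power >80"%, without sidedness. Section 8.3.1 says "A probability of <0.05 will be considered statistically significant for all tests", also without sidedness. Section 8.3.3 plans a linear mixed model for repeated measurements with a random effect for cluster. No section mentions degrees of freedom, a t reference distribution or a small-sample correction.

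**The concern.** Women are allocated by centre, so the error in the treatment comparison is dominated by variation between centres. That variation is estimated from six values, or five if a centre is lost. A normal critical value of 1.645 assumes it is known. With 4 df the one-sided 5% critical value is 2.13, and with 3 df it is 2.35.

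The plan therefore cannot have both the stated power and a true 5% error rate on its own inputs. If the test holds 5%, power is lower than stated. If 1.645 is applied to a statistic with 4 df, the one-sided error is about 8.8% (about 9.9% on 3 df).

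The stated power supports the choice of 288 women and the assurance that the trial could survive losing a centre. A reader who believes the trial had 91% power would take a null result as stronger evidence of no effect than the design supports.

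**Working it through.** **Inputs.** Difference 6 points (4.3); SD 7 (8.4); ICC 0.1 (4.3, 8.4); 40 evaluable women per centre (8.4); 3 v 3 centres, or 2 v 3 after a loss (4.3); one-sided 0.05 (4.3, 8.4). The six centres are taken as independent units, as in the plan's own calculation.

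**Standard error, 3 v 3.** Design effect = 1 + (40 − 1) × 0.1 = 4.9. With 120 women per arm, SE = 7 × √(2 × 4.9/120) = 2.00. Difference/SE = 6/2.00 = 3.00.

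**Standard error, 2 v 3.** SE = 7 × √(4.9 × (1/80 + 1/120)) = 2.24. Difference/SE = 6/2.24 = 2.68.

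**Reproducing the plan (normal test).**
- 3 v 3: Φ(3.00 − 1.645) = 91.2% (stated 91%).
- 2 v 3: Φ(2.68 − 1.645) = 85.0% (stated 85%).
- 30 per centre, 3 v 3: difference/SE = 2.91, giving 89.7% (stated 89%).

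The section 8.4 tables follow the same formula to within about 0.02. For 6 points, SD 7 and ICC 0.1 at 20, 30 and 40 per centre it gives 0.867, 0.897 and 0.912, against tabulated values of 0.87, 0.89 and 0.91. A t on 4 df would give 0.73, 0.77 and 0.79. A two-sided normal test would give 85.1% and 76.5%, which also do not match.

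**Same inputs, non-central t on (centres − 2) df.**

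| Scenario | df | Stated | One-sided 0.05 | Two-sided 0.05 |
|---|---|---|---|---|
| 3 v 3, 40 per centre | 4 | 91% | 79.1% | 61.9% |
| 2 v 3, 40 per centre | 3 | 85% | 65.6% | 45.3% |
| 3 v 3, 30 per centre | 4 | 89% | 77.0% | 59.5% |

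Simulating a t-test on centre means (200,000 runs) gave 79.0% and 65.6% one-sided for the first two rows.

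**Can more women per centre protect against losing one?** As the number per centre grows without limit, the variance of a centre mean falls only to 0.1 × 7² = 4.9. For 2 v 3 centres, SE then tends to √(4.9 × (1/2 + 1/3)) = 2.02, difference/SE = 2.97, and power on 3 df tends to 72.8% one-sided.

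**Sensitivity to the ICC** (40 per centre, one-sided, t-based):

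| ICC | 3 v 3 | 2 v 3 |
|---|---|---|
| 0.01 | 99.8% | 97.9% |
| 0.05 | 93.2% | 83.0% |
| 0.1 | 79.1% | 65.6% |
| 0.2 | 58.0% | 46.1% |
| 0.3 | 46.0% | 36.4% |

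**The listed effect size.** 6/7 = 0.86, not the 0.7 in section 4.3. With 0.7, the normal formula gives 78.9% (3 v 3) and 70.7% (2 v 3), which are not the stated figures. The t gives 64.5% and 51.7%.

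**The case against.** **It is not an arithmetic error.** The plan's figures agree with one another under one formula. What is at issue is the reference distribution. The documents name only the software and a cluster-randomised design, so the normal test is inferred from the match. This stands as a point about description. It does not rescue the figures, since no t-based calculation on these inputs reproduces them.

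**The full design barely misses 80%.** Power is 79.1% at ICC 0.1 and 93.2% at ICC 0.05, and the plan cites ICCs from 0.007 to 0.3. This stands, and it works in both directions: power is 58% at 0.2. The plan itself chose 0.1. Retaining all 48 women per centre would give 80.1%, but the plan assumes 20% loss.

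**79% is not the power of the planned analysis.** The plan has five time points and a repeated-measures model, whereas both its calculation and this one compare a single time point. A reader might infer that the trial will have only 79% power. The documents do not support that. Baseline adjustment or repeated measures may recover power, but no correlation is stated, so the amount cannot be calculated. The supportable statement is that 91% and 85% do not follow from the stated inputs.

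**Two-sided figures are conditional.** A reader might take 62% and 45% as the true power. Sections 4.3 and 8.4 say one-sided and the alternative hypothesis is directional. The synopsis and section 8.3.1 are silent, not contradictory, so these figures apply only if the final test is two-sided.

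**The details could go in the SAP.** Section 8 defers to a binding analysis plan to be finalised before database lock, and a df method could be specified there. That would settle the analysis, but not the power already stated.

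**Conclusion.** The stated 91%, 85% and 89% rest on a one-sided normal test that six centres do not justify. On the plan's inputs, one-sided power at a true 5% level is about 79% for the full design and about 66% with one centre lost. The first is a narrow miss of the 80% target and depends on the ICC. The second is the material failure: at ICC 0.1, the stated reason for moving from 30 to 40 women per centre is not achieved, and no number of women per centre would achieve it.

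These figures assume 6 points, SD 7, ICC 0.1, 40 evaluable women per centre, one time point and no credit for baseline. If the listed effect size of 0.7 is the intended one, they fall to about 64.5% and 52%. A reader might conclude that more women are needed. That does not follow, because the limit lies in the number of centres and the inputs are not yet reconciled.

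**What to change.** Keep 288 women, and make these changes:

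1. Reconcile the effect size of 0.7 in section 4.3 with 6 points and SD 7 (0.86) before restating any power.
2. Recompute section 4.3, the section 8.4 tables and the synopsis with a non-central t on (centres − 2) df, across the tabulated ICCs and for both 3 v 3 and 2 v 3 centres.
3. Restate or qualify the claim of more than 80% power and the assurance about losing a centre.
4. State the same sidedness in the synopsis and sections 4.3, 8.3.1 and 8.4.
5. In section 8.3.3, specify a small-sample df method for the mixed model, such as Kenward-Roger, Satterthwaite or a t on (centres − 2) df, so that the test holds 5% and matches the stated power.
6. If power is credited to baseline adjustment or repeated measures, state the assumed correlation.

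The cost is protocol and SAP wording, a recalculated set of tables and a less favourable stated power. No further participants are needed.

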#### 4.4 Randomization

We will use matched randomization to ensure that the two groups are balanced in terms of population size coverage and geographical area (urban/rural). This will be performed by manually creating 2 groups, each of 3 healthcare centers, based on their population size coverage and geographical area followed by randomly assign the intervention and comparison group to the 2 balanced groups. The randomization will be performed before the intervention begins and it will be carried out by ITM's staff.

Due to the nature of this research and the impossibility of masking the intervention program, this study will not be blinded. Anyhow, to ameliorate the risk of bias, the cluster randomization design was chosen to avoid contamination of information between the participants per healthcare center.

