| OBJECTIVES AND OUTCOMES                    | This study aims to develop, implement, and evaluate a long-term program (KIS-Antwerp) focused on the prevention of type 2 diabetes mellitus (T2DM) and gestational diabetes (GDM) of women through healthy lifestyle promotion. The primary outcome is a healthy lifestyle score measured by closed-ended questionnaire. Secondary outcomes include anthropometric (weight, body mass index and waist circumference), clinical indicators (blood pressure and glycemia) and other dietary and physical activity questionnaires.                                                                                                                                          |
| INCLUSION & EXCLUSION CRITERIA         | 
To be eligible, study participants must meet the following criteria: Non-pregnant and pregnant (first trimester) women of reproductive age (18-49 years) who have not yet been diagnosed with type 1 diabetes or T2DM.
 
Exclusion criteria entail: Pregnant women with active GDM; Children and adolescents <18 years old; men; women of reproductive age with chronic conditions (e.g. chronic kidney disease); living outside the catchment area of the 6 healthcare centers; women without a permanent home or identified physical address; planning to move elsewhere in the following 2 years; women that do not provide a written informed consent
 |
| SCREENING, RECRUITMENT & RANDOMIZATION | Women of reproductive age (pregnant and non-pregnant) will be recruited primarily through the healthcare centers in Kisantu health district as they attend frequently to healthcare centers due to general consultations. The study is based on a hierarchical design where 2 groups of 3 healthcare centers balanced in population size coverage and geographical location are the units that are randomized to the intervention and comparison group through an algorithm allowing stratified allocation.                                                                                                                                                              |

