### Part 1. Research participant information form

This section will compromise a legitimate description of the purpose of the study, the procedures to be followed whereby detailed information of the activities and examinations that will take place will be provided. Also, it will explain the risks and benefits of participating in the study, as well as the compensation and insurance of the study. The form will also include information regarding privacy and data protection, also it will mention that the study was reviewed and approved by the Ethics Committee of the ITM and the local authorities of DRC. Moreover, study participants (or guardians) will be informed that participation in the study is completely voluntary and can withdraw from the study at any time without any negative consequences. Details regarding the contact person in case of questions will be also given.

This study informed consent is based on individuals capable of giving informed consent. For those unable of giving informed consent, we ensure that a legally authorized representative of this person has given permission and this permission takes account of the participants previously formed preferences and values. Minors (<18 years old) are not allowed to participate in this study. Moreover, this study has requested and obtained the permission of the gatekeeper, in this case Zones de Santé (health district) to enroll clusters (healthcare center) during the field visit happened 1st May – 9th May, 2021. Lastly, no opt-out procedures will be stated as this research does not entail any biological residuals nor other type of remaining material such as audio-recordings.

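### Only two hand-formed groups of three centres are randomised, so two allocations are possible, while the power calculation and primary model count three independent clusters per arm

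*Combined protocol and SAP*

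**What the plan says.** Three places in the protocol describe the same allocation.

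- Section 4.4 describes "manually creating 2 groups, each of 3 healthcare centers, based on their population size coverage and geographical area". A single random step then decides which ready-made group goes to which arm.
- Section 4.3 states that "1 group of 3 healthcare centers will be randomly allocated to the intervention group", with the other group going to comparison.
- The Synopsis (screening, recruitment and randomization) says the two groups "are the units that are randomized to the intervention and comparison group through an algorithm allowing stratified allocation". Its design row speaks of a "matched cluster-randomized controlled trial involving 6 healthcare centers".

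Elsewhere a cluster is a single healthcare centre (Section 5.2, Part 1). Section 4.3 counts 48 women per cluster and 144 per arm, so three clusters per arm, and considers losing one (2 against 3). The tables in Section 8.4 use the same structure. Section 8.3.3 fits linear mixed models with a random effect for clusters and mentions no level for the group of three. Section 8.3.1 sets significance at p<0.05. I found no mention of the two-allocation limit, of a randomisation-based test, or of a small-sample correction.

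**The concern.** Two centres in the same group can never fall in different arms. The randomised units are the two groups, but the standard error is built from variation between centres within each arm. That variation contains nothing about differences between the groups, because group and arm are the same thing. If the three centres of a group share some influence on lifestyle scores other than population size and urban/rural setting, it is added to the treatment effect and the model cannot see it.

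The Synopsis adds a smaller conflict. It refers to an algorithm for stratified allocation, while Section 4.4 describes manual grouping and one assignment. With two units there is nothing left to stratify.

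At stake are the causal reading of the primary result and the credibility of its p-value. Allocation cannot be repaired after the event.

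**Working it through.** **Inputs.** Difference 6 points, 3 clusters per arm, one-sided 0.05 (Section 4.3); SD 7, ICC 0.1, 40 evaluable per cluster (Section 8.4). Section 4.3 also lists an effect size of 0.7, whereas 6/7 = 0.86. The stated power matches SD 7, so I use that.

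**1. Reproducing the stated power.**

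- Design effect = 1 + (40 − 1) × 0.1 = 4.9.
- Effective n per arm = 120/4.9 = 24.5.
- SE = 7 × √(2/24.5) = 2.00; 6/2.00 = 3.00.
- Power = Φ(3.00 − 1.645) = 0.912 (stated 91%).
- With 2 against 3 clusters: SE = 7 × √(4.9/80 + 4.9/120) = 2.24; power = Φ(2.68 − 1.645) = 0.850 (stated 85%).
- The two-sided version gives 0.851 and does not match.

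The stated figures are therefore one-sided, use normal critical values, and take three independent clusters per arm. Using 48 × 0.8 = 38.4 evaluable per cluster still gives 91%.

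**2. Counting allocations.** The smallest one-sided randomisation p-value is 1 divided by the number of equally likely allocations.

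| Scheme | Allocations | Smallest one-sided p |
|---|---|---|
| Two fixed groups of three (as written) | 2 | 0.50 |
| Three matched pairs | 2³ = 8 | 0.125 |
| Any 3:3 split of six centres | C(6,3) = 20 | 0.05 |
| 3:3 splits that meet balance limits | fewer than 20 | above 0.05 |

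None is below 0.05.

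**3. Power with a small-sample test.** Six centres compared as two samples of three give 6 − 2 = 4 degrees of freedom. With the same noncentrality of 3.00:

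- one-sided, critical t = 2.132: power 79%;
- two-sided, critical t = 2.776: power 62%;
- three pairs, 2 degrees of freedom, one-sided, critical t = 2.920, no precision gained from matching: power 62%.

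**4. Illustration of the shared-group risk (assumption).** The documents give no correlation at the level of the group. Hold the total ICC at 0.1 and let a part ρ be common to the three centres of a group.

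- True variance of the difference = 2 × 49 × [ρ + (0.1 − ρ)/3 + 0.9/120].
- The centre-level analysis omits the leading ρ.
- At ρ = 0.02 the true SE is 2.30 and the SE the analysis sees is 1.83.

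| ρ | One-sided type I error, z | One-sided type I error, t on 4 df |
|---|---|---|
| 0 | 5.0% | 5.0% |
| 0.01 | 7.2% | 6.6% |
| 0.02 | 9.6% | 8.3% |
| 0.05 | 17% | 14.5% |

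The trial data cannot estimate ρ.

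**The case against.** The strongest reply is that the planned analysis is a model, not a randomisation test. With three centres per arm, the between-centre variance within arms can be estimated, and a centre-level mixed model is defensible if centres are exchangeable given the matching factors. That stands. A reader might infer that the trial has in effect one cluster per arm, or that no valid standard error or p-value exists. The documents do not support that: it is true only of inference based on the randomisation, and the 0.50 in the table belongs to a test nobody planned.

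A reader might also infer that group traits such as management or staffing are fully confounded with treatment. No such shared trait is documented. All six centres lie in one health district with a common antenatal strategy (Section 4.1), and peer educators and health professionals are recruited per centre (Section 9). The groups are built to resemble each other, not to be alike inside, so nothing in the text predicts a positive ρ. The score is also taken at baseline and four later visits (Section 5.1). If the model is read as comparing change, stable differences in level largely cancel and differential trends remain. These points reduce the likely size of the problem. They do not make ρ zero or estimable.

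Nor does the plan claim that centres are randomised separately: Section 4.3 says openly that groups are allocated, and Section 8.3.3 is silent on allocation. The mismatch lies in how clusters are counted for power and modelled.

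**Conclusion.** The point holds in this form: two possible allocations, one randomised unit per arm, and power and analysis that take three independent centres per arm without stating the exchangeability assumption this needs. The count of two follows directly from the text and does not depend on how the random assignment is carried out.

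Under the plan's own effect, SD and ICC, the 91% becomes about 79% one-sided or 62% two-sided once the test reflects six centres with 4 degrees of freedom. Those figures also assume ρ = 0. The type I error table is an illustration under assumed values, not a prediction.

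A reader might conclude that randomising centres alone would restore a randomisation basis for significance at p<0.05. It would not: six centres are too few under any of the schemes counted. Centre-level allocation removes the coincidence of group and arm; the inference stays model-based.

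**What to change.** 1. Rewrite Section 4.4 so that centres are allocated. Either list the 20 possible 3:3 splits, keep those within pre-written, loose limits on population and urban/rural balance, and draw one by computer with a recorded seed; or form three matched pairs and randomise within each. The documents give neither population nor urban/rural class per centre, so the number of qualifying splits has to be worked out by the sponsor.
2. Align the Synopsis with Section 4.4, resolving the stratified algorithm against manual grouping, and say what matching means.
3. State in Section 8.3.3 and the SAP that inference is model-based, that it assumes exchangeable centres given the balancing factors, and that no available scheme can reach p<0.05 by randomisation test.
4. Specify a small-sample degrees-of-freedom correction for the cluster-level test.
5. Restate power in Sections 4.3 and 8.4: about 79% one-sided or 62% two-sided for unpaired centres on 4 degrees of freedom, with fewer degrees of freedom if analysed as pairs. Adding centres is the only route to more.

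The cost is a few paragraphs and a short script, possibly slightly looser balance, and a less favourable stated power. No additional participants are needed for items 1 to 4.

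If allocation has already taken place, disclose the two-allocation design and the exchangeability assumption in the SAP, which Section 8 says is finalised before database lock, and still make items 4 and 5.
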